## Abstract

**Background:**

Deficits in executive functioning are of great significance in attention-deficit/hyperactivity disorder (ADHD). One of these executive functions, working memory, plays an important role in academic performance and is often seen as the core deficit of this disorder. There are indications that working memory problems and academic performance can be improved by school-oriented interventions but this has not yet been studied systematically. In this study we will determine the short- and long-term effects of a working memory - and an executive function training applied in a school situation for children with AD(H)D, taking individual characteristics, the level of impairment and costs (stepped-care approach) into account.

**Methods/design:**

The study consists of two parts: the first part is a randomised controlled trial with school-aged children (8–12 yrs) with AD(H)D. Two groups (each n = 50) will be randomly assigned to a well studied computerized working memory training ‘Cogmed’, or to the ‘Paying attention in class’ intervention which is an experimental school-based executive function training. Children will be selected from regular -and special education primary schools in the region of Amsterdam, the Netherlands. The second part of the study will determine which specific characteristics are related to non-response of the ‘Paying attention in class’ intervention. School-aged children (8–12 yrs) with AD(H)D will follow the experimental school-based executive function training ‘Paying attention in class’ (n = 175). Academic performance and neurocognitive functioning (primary outcomes) are assessed before, directly after and 6 months after training. Secondary outcome measures are: behaviour in class, behaviour problems and quality of life.

**Discussion:**

So far, there is limited but promising evidence that working memory – and other executive function interventions can improve academic performance. Little is know about the applicability and generalization effects of these interventions in a classroom situation. This study will contribute to this lack of information, especially information related to real classroom and academic situations. By taking into account the costs of both interventions, level of impairment and individual characteristics of the child (stepped-care approach) we will be able to address treatment more adequately for each individual in the future. Trial registration: Nederlands Trial Register NTR3415.

## Background

Studies show that children with Attention Deficit Hyperactivity Disorder (ADHD) often suffer from deficits in executive functions, such as attentional control, inhibition and working memory [1,2]. Stimulant medication may reduce the behaviour symptoms of ADHD but they can also have serious side effects and the effects on cognitive- and executive functioning remain unclear [3]. It is known that these executive functions play an important role in academic performances [4]. Especially working memory skills are associated with problems in learning and poor classroom behaviour [5,6]. Working memory refers to the function of actively holding in mind and manipulating information relevant to a goal [7]. Individuals with poor working memory functioning are at risk of poor educational progress, over 85% of children with poor working memory have problems in reading or mathematics [8]. Recently, studies have shown that training of the working memory has positive xeffects for children with ADHD, and/or learning disabilities [9,10]. Children who followed the computer-based working memory training program (Cogmed Working Memory Training, 10) not only showed improved working memory abilities over time, but also showed better performance on related executive function tasks such as logic reasoning and response inhibition and still continued to show effects after 3 months [9,10]. Interestingly, Holmes and colleagues [11] examined the effects of this working memory computer-based training on measures of academic ability. Adaptive working memory training proved to be associated with higher achievement on mathematic and working memory tasks immediately and after a period of 6 months. In this study a classroom analogue of a working memory task (e.g. following instructions) was carried out, which showed improvement as well. So far, research aimed to study the effects of working memory training on academic performance is promising [11,12]. However, few studies have paid attention to the transfer effects of working memory training on behaviour in a classroom setting. Recently, Green and colleagues [13] showed that working memory training in children with ADHD leads to significant reductions of ‘off-task’ behaviour during academic task performance. But they also noted that the absence of measurable effects of working memory training on teacher ratings in previous studies is a notable limitation of the training. Also, methodological issues such as information bias using only teacher reports and having a small sample size [12] were limitations in earlier studies. The aim of our first study is to replicate the above results of working memory training in a Dutch population of school-aged children with AD(H)D. Moreover it will add specific information on academic performance and behaviour in a classroom setting. From a clinically point of view it is expected that improved working memory also has positive effects on functioning in daily life, therefore we will also focus on quality of life. Besides replicating and extending the results from earlier Cogmed studies, we also compare Cogmed with an experimental school-based executive function training. We developed this training from a clinical point of view. Cogmed is a licensed intervention which creates significant costs for healthcare institutions, healthcare insurance companies and parents. Also, from clinical practice we know that (special aid) teachers lack knowledge about executive functioning and its relation to academic performance and behaviour in class. For instance, they need more specific information and practical tools to guide these impaired children throughout their school career, as described by Gathercole and Alloway [8]. Cogmed is a core working memory training, not contextual to a school environment, and teachers are not involved in the treatment when following the Cogmed protocol. Our ‘Paying attention in class’ intervention is an executive function training, contextual to the school environment. This will be extensively explained below in the Method section.

### Aims

(1) The aim of the first study is to examine the effects of a working memory – and executive function training on academic performance, neurocognitive functioning, behaviour in class, behaviour problems and quality of life of children with AD(H)D between the age of 8 and 12 years.

(2) The aim of the second study is to investigate which specific characteristics are related to non-response of the ‘Paying attention in class’ intervention. By offering Cogmed to the non-responders, we will obtain insight into the effectiveness of both interventions, taking into account individual characteristics, the level of impairment and the costs (stepped-care approach).

With the result of both studies we hope to obtain more insight in the effective elements of both interventions so that treatment can be more individually tailored in the future.

## Methods/design

### Approval

The ethics approval was obtained from the Medical Ethical Committee (2011_269) at the Academic Medical Centre in Amsterdam, the Netherlands.

### Design

The first study is a randomised controlled trial in which children will be randomly assigned to the Cogmed RM [10] intervention (n=50) or the experimental ‘Paying attention in class’ intervention (n=50). We expect that for some children treatment can not be started immediately after enrollment. They will be placed on a waiting list. An extra measurement of academic performance and neurocognitive functioning (primary outcomes) will be administered for the children on the waiting list, this will be a control group (n=50). The second study partially replicates and also extends the first study. This second study investigates which specific characteristics are related to a non-response of the ‘Paying attention in class’ intervention, which requires 175 children including the 50 children from the first study. Based on ethical considerations, Cogmed RM [10] will be offered to the non-responders of the ‘Paying attention in class’ intervention after the follow up assessment (6 months).

### Setting

We will approach three types of primary schools in the region of Amsterdam, the Netherlands: regular primary, special primary education and special education schools. The research team closely collaborates with expert divisions on Special Education and ADHD of the Bascule, Academic Centre for Child and Adolescent Psychiatry, Amsterdam.

### Recruitment

For this study children will be recruited in two ways. First, children from clinical care can be enrolled by contacting a member of the research team. Second, children can be enrolled by their school. In both cases, recruitment will take place by approaching a principal and/or remedial teacher via email or telephone. A special information meeting will be held to extensively inform the staff and ask for permission to participate in the study. Once a school agrees to participate, we will work with a staff member (usually remedial teacher or school psychologist) to select children that meet the criteria for participation. Then parents of these selected children will be approached and informed by the school staff member, followed by an extra information meeting especially for parents. Parents receive an application package including an informed consent form. Training will be started after the informed consent is signed by both parents.

### Inclusion and exclusion criteria

#### Inclusion

Children participating in this study are between the age of 8 and 12 years and diagnosed with AD(H)D by a professional according to the guidelines of the Diagnostic and Statistic Manual of Mental Disorders DSM-IV [14]. Children with co morbid Learning Disabilities (LD) and/or Oppositional Defiant Disorder (ODD) are included as well. Both children with or without medication (e.g. stimulants) are included. Children with medication are only included when they are well adjusted to their medication, which means they are not participating in a medication trial and type and dosage of medication is unchanged at least 4 weeks prior to the start and during the training.

#### Exclusion

Exclusion criteria are (a) psychiatric diagnoses other than AD(H)D/LD/ODD; (b) Total Intelligence quotient <80; (c) significant problems in the use of the Dutch language; (d) severe sensory disabilities (hearing/ vision problems).

### Randomisation

For the first study, the Clinical Research Unit of the Academic Medical Centre composed a randomisation list, stratified by age. Children will be individually randomised to either the Cogmed RM [10] or ‘Paying attention in class’ intervention group by a researcher independent of the research team. This researcher will subsequently inform the therapist about the allocated condition for each child. The PhD student and research assistant will be blind for the allocation.

### Coaches

Developmental psychologists will be trained as ‘training aides’ according to the Cogmed working memory training protocol. They will also be trained as therapists for the ‘Paying attention in class’ intervention. This training consists of an interactive 3 hour course, provided by a member of the research team. For both interventions the developmental psychologists will receive weekly supervision by a certified Cogmed Coach and clinical staff member of the Bascule in which they can discuss the progress and clinical difficulties.

All supervision sessions will be registered with the aid of a structured format. Also, the trainers will fill out a logbook per child daily, for observations and special circumstances. Finally the Cogmed Training Web and the ‘Paying attention in class’ workbook will be used to monitor the results of the training. These three documents will be used to create a checklist for evaluating treatment fidelity.

### Interventions

#### Cogmed working memory training RM

Cogmed Working Memory Training RM is specifically used for children between the age of 7 and 17 years. It consists of a variety of computerized, game-format, working memory tasks that are adaptive, which means that difficulty level is being adjusted automatically to match the working memory span of the child on each task. The program includes 12 visuospatial and verbal working memory tasks, eight of these tasks (90 trials in total) are being completed every day [10]. The child follows the standard Cogmed RM protocol which means following the computer training program for 5 weeks, 5 times a week, approximately 45 minutes a day. The program is provided via the internet on a laptop and the child is trained individually at school, guided by a trained developmental psychologist. Cogmed is a licensed intervention that entails significant costs for healthcare professionals / institutions, health care insurance companies and (depending on type of health care insurance) also parents. The Cogmed Coach Training costs €950, exclusive of a monthly license fee which is dependent on the amount of licenses used. A user ID for one child costs €99. In some cases the monthly fee and user ID costs are reimbursed by the healthcare insurance but there always is a statutory contribution of €100 (in the Netherlands), which is often paid by parents.

#### Paying attention in class

‘Paying attention in class’ is an experimental executive function training that has been developed by our research team. The child is trained individually for 5 weeks, 5 times a week, approximately 45 minutes a day; the same duration as in the Cogmed protocol. This ‘Paying attention in class’ has three aims. First of all, the most important aim of this intervention is to offer psycho education about executive functions that are related to classroom behaviour. By making children more aware of these executive functions needed for adequate classroom behaviours, they obtain more insight in their own learning behaviour. The psycho education addresses five executive functions that are important in a learning situation, namely: paying attention, planning skills, working memory, goal-directed behaviour and metacognition. It will be offered through a MP3 player, based on a ‘brain castle’ theme in which specific compensatory strategies and pitfalls are explained to the child. Every session starts with psycho education that is related to one of the above mentioned executive functions. After hearing this, the child is asked to make a neuropsychological - and school task related exercise in which the psycho education has to be applied. The second aim of this intervention is to train working memory functions. This is done by three adaptive working memory tasks: one visual-, one verbal-, and one instruction paradigm task (30 trials in total). The child will be encouraged to use the compensatory memory-strategies from the psycho education. The third and final aim of this intervention is to make a transfer to a classroom-situation, this will be achieved through several ways. First of all, the strategies introduced through the psycho education as described above will be illustrated and practiced by performing school related tasks. Second, the child brings a registration card to class that reminds him/her of the practiced skill of the day (for example, ‘I repeat what is said’). This card includes the name of the specific compensatory strategy. By using a registration card, the child will be reminded what to practice in the classroom. Also it will inform the teacher about the specific executive function and strategy that is practiced on that day so that he/she can reward the child for applying it in class. Finally, to optimize the transfer from the training session to a situation in class we closely involve the teacher in the process by informing him/her with the protocol and by giving him/her an active part in the process. The teacher will receive psycho education about the use of executive functions in the classroom through a written manual, which will increase their knowledge how to recognize and stimulate such behaviour in learning situations. The teacher also receives structured observation forms daily in which he/she can record whether the child applies the practiced strategies in class. The ‘Paying attention in class’ intervention is experimental, so the exact costs are unknown, but we are aiming at a price of €25 a workbook. The costs of a ‘Paying attention in class’ training will be equal to that of the Cogmed Coach Training but there will not be a monthly license fee.

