
### Measures and procedures

After written informed consent is obtained, parents will fill out an application package which contains questionnaires of demographic and background information such as previous care and medication use. The measurements of academic performance and neurocognitive functioning (primary outcomes) are administered in a child face-to-face meeting which takes place at three consecutive moments: at baseline, directly after treatment and 6 months after treatment. The test battery that will measure academic performance consists of an automated math [15], a spelling skill test [16] and technical literacy [17] test. The neurocognitive functioning test battery consists of tests that measure attention [18], verbal [19,20] and spatial working memory [21], inhibition [20], planning and goal-directed behaviour [22]. Also, both parents and teachers fill out the ‘The Behaviour Rating of Executive Functions’ [23] questionnaire. The secondary outcome measures of this study are behaviour in class, behaviour problems and quality of life of the children. This will also be measured at the three consecutive moments mentioned above. Behaviour in class will be reported by the teacher using the ‘Leervoorwaardentest’, a questionnaire [24]. Both teacher and parents will rate behaviour problems using ‘The Child Behavior Checklist for Ages 6–18 [25] and ‘Teacher’s Report Form for Ages 6-18’ [26]. Before training is started, the Diagnostic Interview Schedule for Children [27] and Social Communication Questionnaire [28] is administered to parents to rule out other behavioural problems or psychiatric problems that meet exclusion criteria. Finally, quality of life is measured by using the Kidscreen-27 [29] questionnaire and is completed by parents and the child. All tests and questionnaires have been selected based on results from a small pilot study and clinical experience. Most of the tests and questionnaires are in line with other relevant international literature. Other aspects that were taken into account were duration of administration, variety of neurocognitive tests that can establish possible near and far transfer effects and methodological points such as presence of Dutch norms and test-retest reliability. Table 1 gives an overview of all the assessments and outcome measures.

**Table 1 T1:** Outcomes measures

	**Measure**	**Informant**	T1	T2	T3

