*Primary outcomes*	*Creature counting:* subtest of Test of Everyday Attention for Children [18], measures attentional control and switching	child	*	*	*
	*Score!:* subtest of Test of Everyday Attention for Children [18], measures sustained attention	child	*	*	*
	*Digit span:* subtest of Wechsler Intelligence Scale for Children-III [19], measures verbal working memory	child	*	*	*
	*Span board:* subtest of Wechsler Non Verbal [21], measures visual working memory	child	*	*	*
	*Word list interference:* subtest from Nepsy-II-nl [20], this subtest is designed to asses verbal working memory, repetition and word recall following interference.	child	*	*	*
	*Six part test:* subtest from Behavioural Assessment of the Dysexecutive Syndrome for Children [22], measures planning, task scheduling and performance monitoring	child	*	*	*
	*Inhibition:* subtest from nepsy-II-nl [20], measures the ability to inhibit automatic responses in favor of novel responses and the ability to switch between respons types.	child	*	*	*
	*Behaviour Rating of Executive Functions (BRIEF):* 70 item questionnaire designed to assess executive functioning in the home and school environments [23]	parent/teacher	*	*	*
	*Dictation (PI dictee,* 16): measures spelling skills	child	*	*	*
	*Automated math (Tempo Test Automatiseren,*15): measures degree of automation of addition, subtraction, multiplication and division.	child	*	*	*
	*Speed reading (Een Minuut Test,* 17): measures technical literacy	child	*	*	*
	*Comprehension of instruction:* subtest from nepsy-II-nl [20], measures the ability to receive, process and execute oral instructions of increasing syntactic complexity.	child	*	*	*
*Secondary outcomes*	*Learning conditions test* (Leervoorwaarden test, 24): 70 item questionnaire that measures directly and indirectly learning conditions as concentration, motivation, work rate, task orientation, working according to a plan, persistency, social position in class and relationship with peers and teacher.	teacher	*	*	*
	*Child Behavior Checklist for Ages 6–18 (CBCL/6-18, 25*): 113 item questionnaire designed to measure behaviour problems.	parent	*	*	*
	*Teacher’s Report Form for Ages 6–18 (TRF,* 26): 113 item questionnaire designed to measure behaviour problems.	teacher	*	*	*

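### The teacher-rated BRIEF is a primary outcome, although the teacher is an informed part of the intervention in one arm only

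*Protocol article*

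**What the plan says.** Table 1 (Measures and procedures) lists 12 measures as primary. Eleven are performed by the child. The other is the BRIEF, a "70 item questionnaire designed to assess executive functioning in the home and school environments", with parent and teacher as informants at T1, T2 and T3. The text of that section agrees with the table: "Also, both parents and teachers fill out the" BRIEF comes before the secondary outcomes are introduced. The learning conditions test and the TRF, also completed by the teacher, are secondary.

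Under Interventions, the teacher has a role in the 'Paying attention in class' arm: "we closely involve the teacher in the process by informing him/her with the protocol and by giving him/her an active part in the process". The means are set out. "The teacher will receive psycho education about the use of executive functions in the classroom through a written manual", the child's card tells the teacher which strategy is being practised that day so that its use can be rewarded, and "The teacher also receives structured observation forms daily in which he/she can record whether the child applies the practiced strategies in class". For the comparator, the Background states that "teachers are not involved in the treatment when following the Cogmed protocol".

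On masking, the Randomisation section says only this: "The PhD student and research assistant will be blind for the allocation". It says nothing of teachers or parents.

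**The concern.** A teacher who holds the manual, sees the daily card and receives the observation forms knows which intervention the child is following. That teacher has also been taught to notice the kind of behaviour that the BRIEF asks about. The Cogmed teacher has had no such teaching. The instrument on paper is the same in both arms, but the person who applies it has been changed in one of them.

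At stake is what a difference on this outcome would mean. It would mix change in the child with change in how the teacher perceives and scores the child. As the BRIEF is listed as primary, such a difference could be reported as a primary result.

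**Working it through.** **1. Is this settled by the article, or left to a document not shown?** The primary status, the informants, the time points and the teacher's role in each arm are all stated in the article. Teacher unblinding is not stated in words, but it follows from the manual, card and forms.

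**2. Does the repeated-measures design remove the problem?** Write the observed change on the teacher BRIEF from T1 to T2 as child change plus rater change:

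- 'Paying attention in class': C₁ + R₁
- Cogmed: C₂ + R₂
- Difference in change: (C₁ − C₂) + (R₁ − R₂)

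A rater's constant severity cancels within each child. A shift that arises between T1 and T2 does not. If the teacher is instructed and informed in one arm only, R₁ − R₂ need not be zero, and it has the same form as a treatment effect (arm by time). One rating per child per occasion from the same teacher cannot separate the two terms.

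**3. The plan's own figure.** The Sample size section gives 50 per arm, P < 0.05, 80% power and an effect size of 0.60 (3 points / SD 5 on Digit span). Sidedness is not stated; I take two-sided.

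- Standard error of a difference in SD units: √(2/50) = 0.20
- Power at 0.60: Φ(0.60/0.20 − 1.96) = Φ(1.04) = 85% (84% by t-test)
- n for 80% power: 2 × (1.96 + 0.842)² / 0.60² = 43.6, so 44 per arm (45 by t-test)

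The stated 80% is therefore slightly conservative. This has no bearing on the present point, and only the 50 per arm is used below.

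**4. Illustration of size.** Let b be the rater shift R₁ − R₂ in SD units of the analysed score, with no true effect. The chance of a significant difference is

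Φ(b/0.20 − 1.96) + Φ(−b/0.20 − 1.96).

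| Assumed b (SD) | b/0.20 | Chance of P < 0.05 |
|---|---|---|
| 0 | 0 | 5% |
| 0.1 | 0.5 | 8% |
| 0.2 | 1.0 | Φ(−0.96) + Φ(−2.96) = 17% |
| 0.3 | 1.5 | Φ(−0.46) + Φ(−3.46) = 32% |
| 0.4 | 2.0 | 52% |

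The t-test version gives 16.8%, 31.8% and 50.8% for the last three rows. The values of b are assumptions, as the documents offer none. The formula is symmetric, so it applies equally to a shift against 'Paying attention in class'.

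**5. How much of the primary set is affected?** One of 12 rows, and within that row only the teacher form. No section gives parents a role that differs by arm.

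**The case against.** Teacher involvement is the intended route to classroom transfer, so these teachers cannot be masked, and their ratings carry information that a test session does not. That is right. It is a reason to collect the teacher BRIEF, but not a reason to make it primary.

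The measure is also a small part of the primary set: eleven child-performed tests do not depend on the teacher's judgement, the sample size rests on Digit span, and no section says that one measure alone decides the trial. This stands. A reader might infer that rater bias could carry the whole conclusion, but the article does not show that. How the outcomes are weighed may be set out in a plan that is not at hand.

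A reader might also infer that the bias favours 'Paying attention in class'. The direction is in fact open. A teacher who expects benefit may rate more leniently, while one newly alert to executive problems may report more of them.

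Nor does the article contradict itself. The Background names "methodological issues such as information bias using only teacher reports and having a small sample size" as limitations of earlier work. The criticism is of relying on teacher reports alone, which this trial does not do.

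Finally, children are randomised individually and recruited through schools, so one teacher might rate children in both arms. The article does not say whether this happens. For such a teacher the recalibration from the manual would be shared across arms, but expectation about each child would remain.

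The Strengths and limitations section does warn that the interventions differ in content and applicability. It does not mention raters who are involved in one arm only.

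**Conclusion.** The point holds for the teacher BRIEF as a primary outcome. A between-arm difference in change on that form cannot be attributed to the child alone, and no repeated-measures model will make it so. The 17% to 32% for a shift of 0.2 to 0.3 SD shows how sensitive a comparison of 50 per arm is. It does not estimate how large the shift will be. It assumes a two-sided 5% test, independent children, equal SDs and instruction of the teacher after the baseline rating.

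Two wider conclusions are not supported. The parent BRIEF does not share the problem on the evidence given, as parents have no arm-specific role. And it would go too far to rule out any interpretation of teacher-rated class behaviour: the learning conditions test is the only measure named for that aim, and such a rule would leave the aim without a usable outcome.

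**What to change.** In Table 1, split the BRIEF row into a parent form and a teacher form and report them separately. Keep the parent form as primary and move the teacher form to secondary, beside the learning conditions test and the TRF. Bring the text of Measures and procedures into line. The primary comparison then contains no rating by a person who is part of one arm's intervention.

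Add to Strengths and limitations that the teacher ratings (BRIEF, learning conditions test, TRF) are unblinded, that the rater is involved in the intervention in one arm only, and that they should be read alongside the child-performed tests.

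The cost is one divided table row, a matching edit to the text and one sentence of limitation. One ecologically relevant rating loses its primary status, but it is still collected and reported, so no data are lost.
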